### Qualitative analysis

Audio-recorded remote (telephone or video-conference) interviews will be transcribed verbatim using a professional transcription service and de-identified. Transcripts will be analysed using an inductive thematic approach and will consider the different interviewee characteristics, e.g. the different sites. Qualitative data will be managed using the qualitative software package NVivo to enable initial coding and categorisation of raw data. A thematic framework will be developed based on the research objectives and emerging themes. A proportion of transcripts will be double-coded by an additional researcher, and discrepancies discussed until consensus is reached. A qualitative data collection and analysis plan (QAP) will be developed to detail how the analysis will be carried out.

A triangulation exercise will be carried out to combine quantitative results on fidelity, intervention implementation and usual care with the qualitative data analysis results, using an adapted triangulation protocol technique [63, 64]. Triangulation will allow for an in-depth understanding of the functioning of the intervention, mechanisms and contextual factors and the implementation process to support TIPTOE beyond this trial. The data will support any required refinement of the logic model of change.

### Health economic evaluation

We will carry out a within-trial and lifetime cost-utility analysis (CUA) as well as a cost-consequences analysis comparing the relative costs and outcomes of the TIPTOE intervention with usual care. The within-trial CUA will use the EQ-5D-5L scores from baseline and 6- and 12-month follow-up to calculate the number of quality-adjusted life years (QALYs) gained (or lost) as a result of the intervention using an area-under-the-curve approach. Furthermore, we will collect participants’ healthcare resource use using a CSRI specifically adapted to individuals with OA and MLTCs. Intervention implementation cost will be collected as part of the process evaluation and through discussions with the trial team and will include intervention adaptation and provision, administration, and staff costs for training and delivery. All-cause healthcare resource use (including outpatient visits, inpatient stays and emergency care) will be obtained from NHS Digital and SAIL. Published unit costs will be used to value healthcare resource use at the most current price year. The base case analysis will use the intention-to-treat and linear mixed-effects regression model for repeated measures commensurate with the statistical analysis. Costs and utilities will be presented as point estimates alongside two-sided 95% CIs and *p* values, as well as incremental costs of the intervention compared to usual care. The incremental cost-effectiveness ratio (ICER) of the intervention (expressed as cost in £ per QALY gained) will then be calculated at 12 months from a UK NHS and personal social services (PSS) perspective using the intention-to-treat population as the base case and multiple imputation commensurate with the statistical analysis as sensitivity analysis. Following the within-trial evaluation, a decision analytic model will use the 6- and 12-month healthcare resource use data to extrapolate the longer-term (between 12 months and lifetime) cost-effectiveness of the intervention from a UK NHS and PSS perspective, expressed as cost per QALY gained. We will perform structured literature searches to provide data inputs that cannot be obtained from trial data. A health economic analysis plan (HEAP) will be agreed and signed off prior to database lock. Findings will be reported according to the Consolidated Health Economic Evaluation Reporting Standards (CHEERS) statement [65].

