### Sample size

The TIPTOE trial aims to recruit a total of 824 individuals with knee and/or hip OA and MLTCs. We aim to detect a minimum clinically important difference (MCID) of 0.3 standard deviations (SDs) between the randomised arms in the primary outcome of the MSK-HQ with 90% power whilst controlling the two-sided type 1 error level at 5%. This effect size is consistent with previous research where MCIDs of 0.3 SDs or greater were established for different pain sites [33]. An individually randomised trial with a normally distributed endpoint measured at a single follow-up time point would require 470 participants. Power in repeated measures designs, however, depends on additional factors such as the correlation between repeated measurements [40]: with non-zero correlation the power of a test for mean treatment difference between arms across follow-up time points in a mixed-effects regression model for repeated measures will exceed the power of a two-sample design if the effect size remains the same (0.3 SDs) across follow-up. The latter is unlikely in this study where the difference between arms might ‘peak’ around the time the intervention programme ends and not be fully sustained at 12 months, or conversely, where the full effect might not yet have become manifested at 6 months. Using GLIMMPSE (University of Colorado, Denver, USA) version 3.0.0 with calculations based on the Hotelling-Lawley trace test, which is equivalent to a mixed-model test [41], we studied the power of designs with *n* = 470 under a range of plausible scenarios involving first-order autoregressive correlation structures over time with parameter rho between 0.3 and 0.7 and treatment effects at least the size of the MCID at least at one follow-up time point whilst assuming no difference between treatment arms at baseline due to randomisation. The power exceeded 90% for most of these scenarios and never fell below 83.5%. For most scenarios, between 70 and 90% power was also achieved for testing differences in trend over time between arms.

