### Randomisation method and implementation

Following completion of the baseline measures, participants will be individually allocated in a 1:1 ratio to the TIPTOE intervention or usual care arm using a minimisation algorithm with a random element [49]. Minimisation is based upon self-reported gender (male, female or other), OA site (knee, hip or both) and trial site. Participants and allocated sites will receive email notification informing them of which arm the participant has been randomised to.

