### Statistical analysis

Participant characteristics and baseline data will be summarised descriptively by allocation (intervention or usual care). Data analysts will be blinded to treatment group. The primary analysis will be intention-to-treat (i.e. all randomised participants, regardless of level of adherence to the allocated intervention or ‘contamination’ of usual care, with complete or incomplete follow-up, will be included), and use a partially clustered multi-level model, i.e. a linear mixed-effects regression model with an unstructured covariance structure imposed on the residuals to model the covariance between repeated measures on the same participant [59], and random cluster effects in the intervention arm to account for groups of participants receiving the intervention from the same healthcare team, allowing for heteroskedastic individual-level errors [60]. The model will include categorical time, treatment and their interaction as fixed effects, as well as any factors used to balance the randomisation in the minimisation algorithm. Baseline MSK-HQ will be included in the response variable. This model will be used to compare the mean MSK-HQ scores across follow-up time points between participants receiving the TIPTOE intervention and those receiving usual care using appropriate linear contrasts and a Kenward-Roger approximation to the denominator degrees of freedom [61]. Results will be presented as point estimates alongside two-sided 95% confidence intervals (CIs) and *p* values, as well as variance components and ICCs for healthcare team clustering. Clinical effectiveness will be concluded if the point estimate of the treatment effect favours the intervention, and the 95% CI excludes zero. Similar analyses will be performed for the secondary outcomes.

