In secondary analyses, we will estimate the treatment effect at 6- and 12-month follow-up separately based upon the primary analysis model. We will also assess a potential difference in trend over time between the two arms. The primary analysis will be repeated with a random coefficients model using random effects for each participant’s intercept (and possibly slope) instead of the covariance pattern model described above. A per-protocol or complier average causal effect (CACE) analysis will explore the effect of treatment adherence whilst maintaining groups as randomised. Multiple imputation will be considered as a sensitivity analysis if warranted by the proportion of missing follow-up data. Other sensitivity analysis, such as modelling the outcome variable at baseline as a fixed-effects covariate and fitting a residual correlation structure that is stratified by treatment arm, will be considered. Planned subgroup analyses will involve stratification by (1) type of usual care provided at sites, (2) level of fidelity to the intervention, (3) mode of completion of outcome measures (self-reported versus proxy) and (4) number and type of long-term conditions. Safety outcomes will be tabulated by arm and analysed using logistic regression as appropriate. A comprehensive statistical analysis plan (SAP) will be agreed and signed off prior to database lock. Findings will be reported according to the Consolidated Standards of Reporting Trials (CONSORT) statement [62].

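### As worded, the base-case QALY analysis leaves chance baseline EQ-5D-5L differences in the incremental QALY; adjusting for baseline utility would cost nothing and tighten the estimate

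*Protocol article*

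**What the plan says.** The Health economic evaluation section of the protocol article fixes both the outcome and the model.

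- Outcome: "The within-trial CUA will use the EQ-5D-5L scores from baseline and 6- and 12-month follow-up to calculate the number of quality-adjusted life years", gained or lost "as a result of the intervention using an area-under-the-curve approach".
- Model: "The base case analysis will use the intention-to-treat and linear mixed-effects regression model for repeated measures commensurate with the statistical analysis".

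The model it points to is set out under Statistical analysis: "The model will include categorical time, treatment and their interaction as fixed effects, as well as any factors used to balance the randomisation". The handling of baseline is given next: "Baseline MSK-HQ will be included in the response variable". Neither section says that baseline means are held equal between arms.

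Three other places bear on the reading.

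- Under Statistical analysis, "modelling the outcome variable at baseline as a fixed-effects covariate" appears only among sensitivity analyses to be considered.
- Under Sample size, "assuming no difference between treatment arms at baseline due to randomisation" describes the scenarios used for power, not the analysis model.
- Under Randomisation method and implementation: "Minimisation is based upon self-reported gender (male, female or other), OA site (knee, hip or both) and trial site". EQ-5D-5L is not a balancing factor.

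A HEAP is to be signed off before database lock. It is not shown.

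**The concern.** For the primary outcome, the comparison is of MSK-HQ means across the follow-up visits, so the baseline mean lies outside the contrast. The QALY is different: baseline utility is one of its three components. A model that is serviceable for the first contrast is then applied to a second one that includes a pre-randomisation value.

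If each arm keeps its own fitted baseline mean, a chance difference in baseline utility enters the incremental QALY in two ways. It enters directly through the baseline weight, and indirectly because utility at 6 and 12 months tracks utility at baseline. The incremental QALY is the denominator of the ICER, and cost-effectiveness stands beside clinical effectiveness in the trial's stated objective. At stake is the precision of that estimate, and its accuracy in the one randomisation that is actually observed.

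**Working it through.** **Inputs from the article.** The sample-size section gives 288 analysed per arm and first-order autoregressive correlation with rho from 0.3 to 0.7. The rho range is given for MSK-HQ; using it for EQ-5D-5L is an assumption. The documents give no utility SD, so 0.25 is assumed (range 0.20 to 0.30). Team clustering and missing data are ignored.

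**The plan's own figures.** There is no QALY figure to reproduce. The sample size behind the 288 does reproduce. For 0.3 SD, 90% power and two-sided 5%, the normal approximation gives 234 per arm, 468 in total (plan: 470). With a design effect of 1 + (18 − 1) × 0.02 = 1.34 in the intervention arm, 288 per arm gives 91.4% power (plan: 90%). Allowing for 30% loss, 288 / 0.70 = 411.4, so 412 per arm and 824 in total.

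**Step 1: the contrast.** By the trapezoid rule over one year, QALY = 0.25·u0 + 0.50·u6 + 0.25·u12. If d0, d6 and d12 are the arm differences in mean utility, the incremental QALY is 0.25·d0 + 0.50·d6 + 0.25·d12.

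**Step 2: what the stated model does.** Time, treatment and their interaction give six free means (three visits by two arms). With complete data and a common covariance matrix, the fitted means are the observed means, so the QALY contrast is the raw area-under-the-curve difference. This was checked by generalised least squares on one simulated dataset (SD 0.25, rho 0.5, true value 0.0225, time and treatment terms only). Observed differences were d0 = 0.0429, d6 = 0.0693 and d12 = 0.0643.

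- Free baseline means: 0.25 × 0.0429 + 0.50 × 0.0693 + 0.25 × 0.0643 = 0.0614, SE 0.0169, the same as the raw difference.
- Baseline means constrained equal: 0.0373, SE 0.0121.

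**Step 3: carry-through and variance, in SD units.**

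- Unadjusted variance factor: V = 0.375 + 0.5·rho + 0.125·rho²
- Carry-through per unit of baseline difference: c = 0.25 + 0.50·rho + 0.25·rho²
- Adjusted variance factor: V − c²
- SE = SD × √(2 × factor / 288)

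| rho | V | c | V − c² | Variance ratio | SE unadjusted (SD 0.25) | SE adjusted (SD 0.25) |
|---|---|---|---|---|---|---|
| 0.3 | 0.536 | 0.42 | 0.358 | 1.50 | 0.0153 | 0.0125 |
| 0.5 | 0.656 | 0.56 | 0.340 | 1.93 | 0.0169 | 0.0121 |
| 0.7 | 0.786 | 0.72 | 0.264 | 2.98 | 0.0185 | 0.0107 |

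The ratios and c do not depend on the SD. The square roots of the ratios put the unadjusted confidence interval about 22%, 39% and 72% wider. At rho 0.5 the SEs are 0.0135 against 0.0097 for SD 0.20, and 0.0203 against 0.0146 for SD 0.30. An exchangeable correlation with the same rho gives ratios of 1.67, 2.32 and 3.83.

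**Step 4: size of a chance imbalance.** The SE of d0 is 0.25 × √(2/288) = 0.0208, so its 95% range is ±0.041. Multiplied by c, the shift in the incremental QALY is ±0.017, ±0.023 and ±0.030 at rho 0.3, 0.5 and 0.7. The direct baseline term alone accounts for ±0.010.

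**Step 5: bias or imprecision.** In 10,000 simulated trials (SD 0.25, rho 0.5, true value 0.0225), both the unadjusted and the adjusted estimates averaged 0.0225, with SDs of 0.0169 and 0.0121. Among trials with d0 above 0.02, the unadjusted mean was 0.0403 and the adjusted mean 0.0226.

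**The case against.** The strongest reply is that the article never says QALYs are unadjusted. It is a condensed account, it defers detail to a HEAP that is not shown, and adjustment for baseline utility is just what a HEAP would specify. Keeping baseline in the response is also compatible with a common baseline mean, which is one of the accepted ways to adjust.

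Part of this stands: the HEAP may already settle the matter, and the wording does not exclude a constrained model. But the point does not rest on silence alone. The article names the base-case model and lists its terms. A treatment effect plus a treatment-by-time interaction, with baseline among the responses, leaves the baseline means free unless a constraint is stated. The only mention of baseline as a covariate is an optional sensitivity analysis, and the equal-baseline statement belongs to the power calculation. A HEAP that followed the article literally would inherit the problem.

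It is also fair to say that not all the carry-through is peculiar to the QALY. Of the 0.42, 0.56 and 0.72, only 0.25 is the direct term. The rest (0.17, 0.31 and 0.47) is ordinary persistence of baseline, which affects any follow-up comparison left unadjusted.

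Two stronger readings are tempting and should be resisted. A reader might infer that the ICER is biased by design. It is not shown to be: under randomisation the unadjusted QALY difference is right on average, as Step 5 confirms. A reader might also infer that the imbalance sets the starting point of the lifetime model. The article says only that the decision model will draw on 6- and 12-month resource-use data and on literature inputs. Nothing ties its starting state to arm-specific baseline utility.

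**Conclusion.** The point holds as one of precision and of accuracy given the observed imbalance, not of bias. Read literally, the stated base case lets a chance baseline utility gap into the incremental QALY. Under the assumed correlations, 42% to 72% of the gap carries through, and the variance is about 1.5 to 3.0 times what baseline adjustment would give. Put the other way, adjustment removes 33% to 66% of the variance (1 − 1/1.50 to 1 − 1/2.98).

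These figures rest on three assumptions: that EQ-5D-5L shares the MSK-HQ autoregressive range, that clustering and missing data can be set aside, and that the model is fitted with free baseline means. The absolute QALY figures also need the assumed utility SD. If the HEAP already imposes the adjustment, all that remains is to align the wording. This is a free improvement to a stated objective of the trial rather than an error that invalidates the economic analysis.

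**What to change.** In the Health economic evaluation section and in the HEAP, state that the base-case incremental QALY is adjusted for baseline utility, by one of two routes:

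- in the repeated-measures utility model, constrain the baseline means to be equal between arms and take the area-under-the-curve contrast with d0 = 0; or
- regress each participant's area-under-the-curve QALY on arm, baseline EQ-5D-5L utility and the minimisation factors.

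Use that estimate in the ICER. The change is one sentence in each document before database lock. Baseline EQ-5D-5L is already collected, so it needs no new data, participants or staff time beyond the drafting.

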### Oversight and monitoring

A trial management group (TMG) will meet bi-monthly to review trial progress and recruitment targets. There will also be an external Trial Steering Committee (TSC) providing independent oversight and an Independent Data Monitoring Committee (IDMC) to review participant safety. All members of these committees have signed the respective trial specific charters. The TIPTOE trial team agree to allow trial related monitoring, including audits and regulatory inspections, by providing direct access to source data as required. Participant consent for this will also be obtained as part of the informed consent process.

### Safety

Participants will be asked to use the ‘report a problem’ link on the study website, or to inform their local healthcare professional to report any relevant medical events that occur during their time on the trial (from giving consent to 12-month follow-up). In this patient population, high rates of acute illness resulting in hospitalisation, new medical problems, deterioration of existing medical problems and death are expected. This information will be collected as part of the routine follow-up and will not be subject to serious adverse event (SAE) reporting. We ask for participants to report if they have a fall that results in hospitalisation or an SAE thought to be related to the trial intervention or research procedures. An SAE is defined as any adverse event that (1) results in death, (2) is life threatening, (3) requires hospitalisation or (4) results in persistent or significant disability or incapacity. The site principal investigator will review the event to determine if it meets the trial’s definition of an SAE. If so, an SAE form will be completed by the site team. All safety reports will be reviewed by the central trial team for completeness and uploaded to the trial database.

## Discussion

Knee and/or hip OA affects 1 in 2 older adults, with nearly 7 in 10 OA sufferers having more than one other medical condition. This trial will examine the clinical and cost-effectiveness of the TIPTOE intervention across multiple sites and services in Wales and England. Routine data will be collected throughout the trial to inform healthcare resource use. For participants in England, we will work with NHS Digital to obtain prospective linked Hospital Episode Statistics (HES) data, emergency care data and GP data. For participant in Wales, we will seek to obtain the equivalent data from the Patient Episode Dataset for Wales (PEDW), Outpatient Dataset for Wales (ODW), Emergency Department Dataset Daily (EDDD) and the Welsh Longitudinal GP Dataset (WLGPD). The embedded process evaluation will inform subsequent implementation should the intervention be shown to be clinically and cost-effective.

The SWAP will inform the trial to ensure for maximum inclusivity, whilst the provision of multiple routes of participant identification, various modes of information delivery (written and visual), data collection (online or via telephone) and intervention delivery (face-to-face or video conferencing) from the outset also aims to maximise inclusion. Wales will form a single site under a ‘One Wales’ model facilitating recruitment across Wales regardless of location, an approach which has been successfully implemented previously [66]. Sites in the South East and South West of England, London, and the North will also be opened to recruitment.

Extensive patient and public involvement and engagement (PPIE) input has been employed in the project, following the UK Standards for Public Involvement [67], from the co-design of the TIPTOE intervention through to the development of the trial protocol and patient facing documents and materials. Additionally, the health practitioner training which is overseen by Bridges Self-Management will be co-delivered with an individual living with joint pain. Our PPIE members will continue to support the trial team with ongoing advice and input into recruitment strategies, advertisements and later dissemination planning. Two PPIE members are part of the trial management group. We are utilising the Public Involvement in Research Impact Tool to encourage discussion, collaboration and a transparent approach to public involvement planning and impact reporting in TIPTOE.

The TIPTOE trial will form an evidence base for whether services should integrate this self-management intervention, and the benefits and costs of doing so.

## Study status

This manuscript has been drafted according to version V4.1 (15/07/2024) of the trial protocol and in accordance with the SPIRIT checklist. The trial opened to recruitment in January 2024, with recruitment anticipated to end by March 2025.

## Data Availability

All trial data will be stored on the TIPTOE Research Data Storage space in a secure repository held by Cardiff University. The CTR is a signatory of AllTrials and aims to make its research data available wherever possible. Data requests will undergo a review process to ensure that the proposal complies with patient confidentiality, regulatory and ethical approvals and any terms and conditions associated with the data. On study completion, trial data will be made available upon reasonable request and following CTR data sharing policies. Requests to access the data should be made to the [contact]. The datasets analysed during the current study and statistical code are available from the corresponding author on reasonable request, as is the full protocol.

